### Sample size

Our sample size estimate is based on the primary outcome. Reports of randomized studies of geriatric care transitions interventions have reported 25–45% reductions in hospital readmissions [17, 20, 29]. Based on prior work as well as pilot data gathered within the VHA (unpublished), we postulate that the notification-only group as well as the usual care group will have a 40% readmission rate while the notification-plus-coordination group will have a 26% readmission rate in the 90-day post-discharge period (i.e., a clinically significant 35% reduction).

There are several features of the study that support this large potential effect. First, the targeted patients are at high risk of readmission because they are older veterans who utilize both VHA and non-VHA services, who have been shown in previous studies to have significantly higher readmission rates after acute illness. Second, in contrast to veterans hospitalized in the VHA who routinely receive PACT post-discharge telephone calls and follow-up, this group is naïve to any coordination intervention because PACT teams normally do not respond to non-VHA hospital encounters because they do not know about them. Thus, we postulate more than an incremental effect.

To account for possible dependence of the outcome among patients cared for by the same PACTs (clustering), we estimated the design effect [30] based on an average number of subjects per PACT = 7. Assuming the intraclass correlation is 0.05 (based on pilot data and prior literature [31]), we need to observe a total of 466 patients with non-VHA hospitalizations or ED visits (155 in the notification-plus-coordination group and 311 combined in the notification-only and usual care groups) to detect an effect size of 0.35 with 80% power and a two-tailed test at 5% significance. If the intraclass correlation is smaller (e.g., 0.04), which may be the case for a group of patients whose care is fragmented and perhaps less influenced by primary care team clustering, then the power will be higher.

In order to achieve the target sample size, we will enroll 300 patients at each site, with an estimated 25–30% of enrolled veterans experiencing non-VHA hospital encounters. We anticipate 10–15% attrition due to death or loss to follow up given the average age of veterans in the target population.

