Although this study is conducted within the VHA system, the findings should be applicable to other health systems within the U.S. as well as global health systems. There is nothing inherent in the study design that precludes implementation in other settings. With respect to the informatics systems, ADT systems are widespread in health care systems as they drive many EHR and decision support system functions. Furthermore, patients cross “system” boundaries in every country, including care seeking at public and private hospitals as well as “in-network” and “out-of-network” facilities. Prior studies examining global health systems find a common pattern of poor care coordination [5]. Furthermore, a more recent analysis by Penm et al. [47] found that poor primary care coordination was more likely to occur among patients younger than 65 years. Therefore findings from this study may be applicable to care coordination for age groups beyond older adults.

The study does possess several challenges of note. First, maintaining adequate statistical power will require that a sufficient number of patients experience acute care events outside the VHA. This is not desired, but necessary to observe natural care coordination processes in addition to those influenced by the event notifications. If there are fewer than expected non-VHA encounters, enrollment will need to be increased or the study timeframe will need to be lengthened. This is one reason why we added a second phase to incorporate individuals who are unable to be approached and recruited formally into the study. Such a design is atypical for trials. However, it is impossible to predict a priori which patients will have an acute encounter outside of the integrated VHA health system.

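### Read as written, 300 veterans per site yields about 75–90 coordination-arm index patients (64–81 after attrition), not the 155 the power statement needs

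*Protocol article*

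**What the plan says.** All the figures stand in the Sample size section of the protocol article.

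- **Rates.** "the notification-only group as well as the usual care group will have a 40% readmission rate", and "the notification-plus-coordination group will have a 26% readmission rate in the 90-day post-discharge period".
- **Target.** 466 patients with a non-VHA hospitalization or ED visit, split as "155 in the notification-plus-coordination group and 311 combined in the notification-only and usual care groups", in order "to detect an effect size of 0.35 with 80% power and a two-tailed test at 5% significance". The design effect uses 7 patients per primary care team (PACT) and an intraclass correlation of 0.05.
- **Route to the target.** "we will enroll 300 patients at each site, with an estimated 25–30% of enrolled veterans experiencing non-VHA hospital encounters".
- **Losses.** "We anticipate 10–15% attrition due to death or loss to follow up".

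Three other sections bear on the split. Allocation randomises 25 Bronx and 41 Indianapolis PACTs 1:1 between the two notification arms. Trial design makes Phase 2 a retrospective control group with neither intervention. The Discussion, on the risk of too few events, says of Phase 2: "This is one reason why we added a second phase to incorporate individuals who are unable to be approached and recruited formally". It also foresees more enrolment or a longer timeframe if encounters turn out fewer than expected.

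**The concern.** The required number, the enrolment, the event share and the attrition appear in consecutive paragraphs, and the enrolment is offered as the means of reaching the requirement. Multiplied out, they do not meet. The deficit falls on the coordination arm, the one group that Phase 2 cannot supplement.

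The primary model in Statistical methods compares notification-plus-coordination with everyone else, so the size of that arm largely fixes the precision of the main test. If power is nearer one half than 80%, the postulated 14-point reduction could easily be missed in a trial that the Discussion describes as adequately powered for the added benefit of coordination.

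**Working it through.** **1. The plan's own figure.** Design effect DE = 1 + (7 − 1) × 0.05 = 1.30. With 26% v 40%, two-sided 5%, 80% power and 1:2 allocation:

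- pooled-variance formula: 134 × 1.30 = 174 in the smaller group, about 523 in total;
- unpooled: 125.1 × 1.30 = 163, about 488 in total.

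Neither gives 155/311. Equal allocation gives 176 × 1.30 × 2 = 458, so 466 is closer to a 1:1 total than to a 1:2 total.

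**2. Power formula.** With n1 coordination and n2 comparator patients:

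- SE1 = √{DE × [0.26 × 0.74/n1 + 0.40 × 0.60/n2]}
- SE0 = √{DE × p̄(1 − p̄)(1/n1 + 1/n2)}, where p̄ is the weighted mean rate
- pooled power = Φ[(0.14 − 1.96 × SE0)/SE1]; unpooled power = Φ[0.14/SE1 − 1.96]

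At 155 v 311 and DE 1.30: p̄ = 0.353, SE0 = 0.0536, SE1 = 0.0512. Power is Φ(0.68) = 75% pooled and Φ(0.78) = 78% unpooled. So the stated split falls a little below 80% even if fully accrued.

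**3. Accrual from the stated rates.**

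- Enrolled: 2 × 300 = 600.
- With an index event: 600 × 0.25 = 150 to 600 × 0.30 = 180.
- Coordination arm at 1:1: 75 to 90, which is 52% to 42% short of 155.
- After attrition: 75 × 0.85 = 63.75 (about 64) to 90 × 0.90 = 81, which is 59% to 48% short.
- The notification-only arm has the same expected size, so Phase 2 would have to supply about 221–247 controls to reach 311. It adds nothing to the 155.

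**4. Design effect that fits this accrual.** 66 PACTs give about 33 per arm, so 64–90 patients are about 2–3 per PACT. DE = 1 + (m − 1) × 0.05 is then 1.05–1.09, taken as 1.07.

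**5. Power against the full 311 comparators (pooled / unpooled).**

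| Coordination arm | DE 1.30 | DE 1.07 |
|---|---|---|
| 64 (25%, 15% attrition) | 45% / 51% | 53% / 59% |
| 75 (25%, no attrition) | 51% / 57% | 59% / 65% |
| 81 (30%, 10% attrition) | 53% / 59% | 62% / 67% |
| 90 (30%, no attrition) | 57% / 62% | 66% / 71% |

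Example, 90 v 311 at DE 1.30: p̄ = (90 × 0.26 + 311 × 0.40)/401 = 0.369, SE0 = 0.0658, SE1 = 0.0615. This gives Φ(0.18) = 57% and Φ(0.32) = 62%.

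**6. Can more controls repair it?** With unlimited controls at DE 1.30, power is 52–68% pooled and 61–76% unpooled. At DE 1.07 it is 61–77% pooled and 69–83% unpooled. Only the most favourable corner (90 patients, unlimited controls, small DE, unpooled) passes 80%, and the plan specifies 311 comparators.

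**7. What would reach 155.** Both prospective arms together need 310 index patients. From 600 enrolled that is 310/600 = 52%, or 57–61% allowing for 10–15% attrition. At 25–30% it needs 310/0.30 = 1,034 to 310/(0.25 × 0.85) = 1,459 enrolled.

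**The case against.** The strongest reply is that the percentage is undefined. The section gives no period for it, and Trial design calls the study multi-year. If it were an annual rate (an assumption), the cumulative share is 1 − (1 − r)^years:

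- two years: 44–51%, so 131–153 in the arm, or 112–138 after attrition, still below 155;
- three years: 58–66%, so 173–197, or 147–177 after attrition, which straddles or exceeds 155.

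The rate is also stated for hospital encounters, while the target counts hospitalizations or ED visits. If ED-only visits come on top, the yield is understated. This stands. A reader might infer that the trial is bound to miss 155 whatever the rate means, and the document does not support that. Nor does it supply the annual reading, a duration or a separate ED rate.

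Attrition may not apply in full. The primary outcome comes from exchange, record and data-warehouse sources, so a patient lost to interview can still count. Hence the separate 75–90 and 64–81 ranges.

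The design effect of 1.3 is pessimistic for 2–3 patients per PACT. That also stands, although usual-care clusters may be larger, so both values are shown.

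The contingency in the Discussion does not answer the point. It is triggered by fewer encounters than expected, and here the expected number is itself too small. Condensation is no answer either, because the figures are stated and disagree.

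A reader might also infer that the coordination arm governs every comparison. It does not: Trial design also plans notification-only v control, which does not involve that arm.

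**Conclusion.** The point holds for the text as written. With 25–30% read as the cumulative share of enrolled veterans having an index event, and equal numbers in the two prospective arms, the coordination arm is 42–59% short of 155. Power for the coordination contrast against 311 comparators is about 45–62% at design effect 1.3, or about 53–71% at about 1.07.

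It would be tempting to charge the whole gap from 80% to accrual. That is too strong, because 155 v 311 gives only about 75–78% under the protocol's own inputs.

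The multiplication is certain. The size of the shortfall depends on the cumulative reading, and an annual rate over about three years of monitoring could remove it.

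**What to change.** In the Sample size section:

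1. Define the 25–30%: over what period, hospitalizations only or also ED visits, and before or after attrition. State the planned monitoring duration.
2. Reconcile the resulting yield with 155 in the coordination arm.
3. Give the expected size of each of the three groups, and the power or minimum detectable difference at those sizes, using a design effect that matches the expected number of patients per PACT. Recheck the 155/311 split at the same time.
4. Withdraw the claim that 300 per site achieves the target unless the defined rate supports it, meaning about 52% of enrolled veterans with an index event, or 57–61% with attrition.

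The cost is a rewritten paragraph and a short recalculation. The drawback is that, unless the clarified rate closes the gap, the stated power becomes less favourable, or enrolment or monitoring has to grow.

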### Recruitment

We will employ a number of strategies to maximize recruitment. The VHA Office of Research & Development requires that Veterans first be contacted in writing before being approached by the study team. Using a semi-automated method in which we identify potentially eligible veterans using EHR data in combination with the scheduling system similar to prior VHA studies [32], we will send letters to veterans with upcoming VA primary care appointments whose medical chart pass initial screening. Next we will contact veterans who receive a letter and schedule in person appointments to complete screening and enrollment. We will further contact PACT teams and providers directly. Interested Veterans who inquire during a clinic visit about participation will be able to contact the study team for eligibility screening during business hours and answered by voicemail at all other times.

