### Allocation

We will cluster randomize by PACT team to prevent a team from having patients in both treatment groups and reduce contamination. Prior to initiating enrollment, the lead investigator ([name]) will assign PACTs to notification-plus-coordination or notification-only groups, using lists of computer-generated random numbers in a 1:1 ratio, with separate lists for the Bronx VA and Indianapolis VA, in order to maintain balance in groups within each study site. There are 25 primary care PACTs in the Bronx and 41 in Indianapolis, and each PACT will keep its group assignment for the duration of the study. In Phase 1, enrolled patients will be assigned to notification-plus-coordination or notification-only groups according to their assigned PACT team.

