### Data management

All study data will be captured and stored within the VHA using standard tools available to VHA researchers. Information captured from veterans or extracted from medical records will be stored in a secure study database hosted on a password-protected server accessible only to authorized study personnel. The randomization status for each cluster will be kept in a secure location accessible only to study investigators but not the RAs and project managers to ensure blinding.

The database will contain separate tables that will store individuals’ data pertaining to eligibility, enrollment, activation (e.g., non-VHA acute care events), baseline information, 30-day follow up information, 90-day follow up information, and study completion or withdrawal. The database will enable tracking of individuals who are believed to be eligible and whom the study team mailed information about participation, as well as those who met with an RA but were found to be ineligible for study enrollment. This database will be used to drive trial processes as well as store data for planned analyses, both primary and secondary. Periodic review of data completeness and instruments used to capture data will be performed by the study team to ensure quality of data collection and analysis. Furthermore, prompts will be developed in data entry forms for out-of-range and inconsistent entries, to prompt immediate correction.

Informed consent will be obtained from all participants and confidentiality will be ensured. The database as well as hard copies of patients’ informed consent documents and other study files will be secured and stored according to the regulations of the VHA Research & Development Office, institutional ethics board, as well as the Health Insurance Portability and Accountability Act (HIPAA). Study records will be maintained and expunged in accordance with the VHA Records Control Schedule.

Open-ended interview data will be transcribed and coded by VHA research staff. Codebooks will be developed collaboratively by the investigators, and coding quality will be routinely assessed by the study team to ensure consistency across transcripts. Regular meetings to review transcript snippets and coding progress will ensure harmonization of approaches across coders, and disputes will be resolved by the principal investigator.

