Furthermore, although we considered using a third, “usual care” arm for enrolled patients like most trials instead of the second phase, we ultimately deemed it potentially unethical to deny patients a potentially valuable event notification intervention. Ethical dilemmas with respect to randomization are common in biomedical informatics intervention studies [48], which often require quasi-experimental approaches [49]. Moreover, the number of primary care medical homes distributed across the two sites would limit statistical power if they were divided into thirds for randomization. Therefore we opted to retrospectively use patients who did not enroll in the study or who enrolled but had a non-system encounter outside the prospective monitoring period as a control arm. Doing so enables us to retain the robustness of randomization in arms 1 and 2 while maintaining statistical power with arm 3.

Another challenge for the study will be the implications of the findings. Should the care transitions intervention in combination with event notification prove to be superior, how can the VHA feasibly disseminate this approach? Furthermore, how can health systems economically sustain such an approach? The care transitions intervention requires active monitoring by a social worker or other care coordinator following discharge from the “out-of-network” facility. A home visit and phone monitoring may not be possible in every care transition. A challenge for our team will be to determine under what circumstances a superior but more intense intervention would be cost effective for the VHA or another health system.

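### Veterans are recruited after their PACT's arm is fixed, partly through PACT contact and clinic inquiries; as PACTs can be expected to learn their arm, the randomised comparison of arms 1 and 2 is not fully protected from differential recruitment

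*Protocol article*

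**What the plan says.** All references are to the protocol article.

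- **Allocation.** PACTs are randomised first ("Prior to initiating enrollment, the lead investigator" assigns them), and "each PACT will keep its group assignment for the duration of the study". Veterans come later: "enrolled patients will be assigned to notification-plus-coordination or notification-only groups according to their assigned PACT team".
- **Recruitment.** The main route does not depend on arm: "we will send letters to veterans with upcoming VA primary care appointments whose medical chart pass initial screening". Two further routes run through the clinics. One is direct contact: "We will further contact PACT teams and providers directly". The other is for "Interested Veterans who inquire during a clinic visit about participation", who may then approach the study team for screening.
- **Data management.** Cluster status is kept in a place "accessible only to study investigators but not the RAs and project managers to ensure blinding".
- **Study setting and Interventions.** The rationale for clustering anticipates that providers may notice the care transitions service. Home visits and calls in arm 2 are recorded as clinical notes in the VA EHR.
- **Discussion.** Of the retrospective control arm it says: "Doing so enables us to retain the robustness of randomization in arms 1 and 2 while maintaining statistical power with arm 3".

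**The concern.** When clusters are allocated first and individuals recruited afterwards, randomisation balances the clusters. It balances the patients only if entry into the trial does not depend on arm. A team that knows its veterans will receive home visits may encourage different veterans to join, or encourage them more strongly, than a team that can offer only a notification.

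Arm 3 is identified retrospectively and is not randomised, so arm 2 against arm 1 is the only randomised contrast in the trial. Frailer veterans entering arm 2 would hide a benefit, and more engaged or healthier ones would create or inflate one. Intention-to-treat analysis keeps veterans in their assigned group but does not correct who entered it.

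**Working it through.** The plan gives no figure on this point, so the check is mainly a reading of the sections together.

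**1. Order of events.** Arms are fixed before enrolment (Allocation). Anyone who knows a PACT's arm therefore knows the arm of every veteran that PACT might send.

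**2. Can the PACT influence entry?** The main list-and-letter route does not need the PACT. Direct contact with teams, and inquiries at clinic visits, both allow a provider to encourage a veteran before a research assistant is involved. The text does not say that PACTs nominate patients, and it does not exclude it.

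**3. Can the PACT know its arm?** Not from the randomisation list, which only investigators can see. Not from the event note either, because PACTs in both arms 1 and 2 review and co-sign it. The coordinator's notes in arm 2 do distinguish the arms, but they appear only after an enrolled veteran has a non-VHA event.

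**4. How quickly?** Inputs: 300 veterans per site at two sites and 25-30% with an event (Sample size); 25 + 41 = 66 PACTs (Allocation).

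- Enrolled per PACT: 600 / 66 = 9.1.
- Activated per PACT: 9.1 × 0.25 = 2.3 to 9.1 × 0.30 = 2.7, before attrition.

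An arm-2 team would thus see coordinator notes for only two or three veterans over the whole study. Awareness would build gradually and would not be present at the start. It matters to the extent that recruitment is still open by then. The article does not state the overlap. The Discussion does say that enrolment may be increased or the study lengthened if events are too few, which would increase it.

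**5. Do the safeguards close the gap?** Blinded assistants cannot undo selection that took place before they met the veteran. The covariates in Statistical methods are optional and address only measured differences. The examples listed there do not name the functional and mental-status measures collected at baseline, and some (discharge diagnosis, length of stay, non-VHA hospital) arise only at the index event.

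**6. Scale, on assumed inputs.** The Sample size section gives 40% without the coordination intervention and 26% with it. The ratio is 0.26 / 0.40 = 0.65, and the difference is 14 points. Assume that a share f of arm 2 is provider-prompted, that these veterans' untreated 90-day risk differs from 40% by d, that arm 1 has no such selection, and that the ratio 0.65 applies to everyone. Neither f nor d is in the document.

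Untreated arm-2 risk = 0.40 + f × d. Observed difference = 0.40 − 0.65 × (0.40 + f × d).

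| f | d | Untreated arm-2 risk | × 0.65 | Observed difference |
|---|---|---|---|---|
| 0.10 | +0.15 | 0.415 | 0.270 | 13.0 points |
| 0.30 | +0.15 | 0.445 | 0.289 | 11.1 points |
| 0.10 | −0.15 | 0.385 | 0.250 | 15.0 points |
| 0.30 | −0.15 | 0.355 | 0.231 | 16.9 points |

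If the intervention had no effect, the spurious difference would be f × d. With d of 15 points this is 1.5 to 4.5 points. Over f = 10-50% and d = 5-20 points it runs from 0.10 × 5 = 0.5 to 0.50 × 20 = 10 points, that is 0.5 / 14 = 4% to 10 / 14 = 71% of the planned difference. A range this wide shows that the inputs decide the answer. It is not evidence that selection occurs.

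**The case against.** The strongest reply is that the plan already limits the risk. Cluster status is open only to investigators, which on its wording excludes the PACTs as well as the assistants. The main route is a common list with letters, and eligibility criteria are the same for both arms. Baseline function, mental status and high-risk medications are collected, and imbalanced covariates are to be added to the model. Contact with PACTs may mean no more than informing clinics that the study exists. What PACTs are told is also detail that a condensed article may leave to the full protocol.

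Much of this stands. A reader might infer that the PACTs are unblinded from the start, that allocation cannot be hidden from them, or that they select and refer frail patients. The document supports none of these. No passage says that teams are told their arm, co-signing happens in both arms, and nomination of patients is not mentioned. It would also be wrong to say that the data management rule leaves PACTs out of account.

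Two things remain. Restricting the list does not stop a team from learning its arm from coordinator notes in its own EHR. And PACT contact is a recruitment route that the article states, not a detail it leaves out.

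**Conclusion.** The point holds in a limited form. Allocation precedes recruitment, PACT contact and clinic inquiries are among the recruitment routes, and arm-2 teams can be expected to learn their arm as coordinator notes accumulate. Encouragement to join could therefore come to differ by arm, so the robustness claimed in the Discussion for arm 2 against arm 1 is not fully secured.

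The conclusion rests on two inferences: that PACTs read the coordinator notes, and that recruitment is still open when they do. Both are reasonable, and neither is stated. The size and direction of any bias cannot be derived from the document, and the figures above are illustrations only. The list-based main route and the blinded assistants make this a cheap improvement worth making, not a demonstrated bias.

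**What to change.** 1. In the Recruitment section, limit contact with PACT teams and providers to identical, neutral information in both arms, with no nomination of patients, and keep invitation from the common EHR and scheduling list as the recruitment route.
2. Where clinic or provider-prompted inquiries are accepted, record the recruitment route at screening. The study database described under Data management already tracks mailed veterans, so this is one added field.
3. Prespecify a sensitivity analysis of arm 2 against arm 1 restricted to list-invited veterans.

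The cost is the extra field, a common text for PACT contact, and a slightly smaller set for the sensitivity analysis. Closing the clinic routes altogether would go further, but it trades against recruitment and is not needed to meet this point.
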